## 3.2 Study design

This study is a single-center, prospective, single-blind, randomized, controlled trial. It aims to assess the efficacy of VR as a more effective preparation method for in-person simulation trainings, compared to e-learning. The focus is on improving physicians' trauma CPR management skills.

All recruited participants will watch a 60-minute video to learn about the requirements, steps, and other important information about this study. Furthermore, this introductory video will give an overview of management strategies for trauma patients going into cardiac arrest in an in-hospital setting and provides links to the guidelines (30–32) on which this study is based. It also indicates that knowledge of the content of the guidelines is a prerequisite for Phases 2 through 3. This video can be viewed as often as desired throughout the study. Participants will also be required to complete the electronic Questionnaire 1 (Additional file #2) prior to randomization, which assesses participants' baseline characteristics (including the German versions of the "Openness to Experience" subscale of the 100-item HEXACO-PI-R test (33,34) and the Technology Readiness Scale (35)).

Each participant will then complete either the e-learning course (control group) or the VR training simulations (intervention group) over a two-week period, both focusing on the same content. Both groups will spend approximately the same amount of time learning the same content, which will prepare the participants for the assessment in the simulation session. If participants do not complete the entire e-learning course or all four VR simulations, they will be dropped from the study.

After Phase 2, all participants will attend the simulation session and will be evaluated in the role of medical team leader of a standardized TCA scenario (Phase 3).

In addition, each participant will be required to complete Questionnaire 2 (Additional file #3) immediately following the simulation session in Phase 3. Only the intervention group will be required to complete the VR system usability portion of this questionnaire. The system usability scale (SUS) (36,37) will be translated and used in German.

[figure not shown]

**Figure 1.** The course of events during the study.

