### 3.2.2 Control and Intervention

The control group will complete an e-learning course over a two-week period in preparation for the subsequent simulation session, which will teach the same content as the VR simulation software in the intervention group.

Both e-learning and VR have the limitation that manual skills cannot be practiced. The content will therefore focus on procedural processes and guideline adherence in the context of trauma patient care and traumatic cardiac arrest in shock rooms. In addition to basic life support (BLS) and ALS, there will be additional specific learning content (15) such as structured patient assessment (xABCDE approach) and special care strategies for this unique patient population.

The e-learning course will also focus on basic principles of crew resource management (CRM) and related communication skills (15,39), such as closed-loop communication. It has also been shown that cognitive aids such as checklists, flowcharts, or mnemonics can be very helpful to HCPs in such settings, and their use is recommended (20). Accordingly, their use will also be an essential part of this e-learning course.

Once enrolled, all participants randomized to this group will receive access information for the course, which, like the VR training, will be conducted in German and must be completed within 2 weeks.

Participants randomized to the intervention group will learn and practice the exact same content using a VR training environment co-developed by the research team of this study. The developed software with its four TCA scenarios must also be practiced over a period of 2 weeks, which corresponds to the same time and learning effort as the e-learning course.

In order to make the VR training sessions as efficient as possible, it is necessary to provide the participants with an additional orientation module that must be played before the VR training sessions begin. This additional module will take about 20 minutes to play once to familiarize the participants with the technical features of the VR headset and the controllers and to keep their focus on the medical content instead of the technical features. The developed software will be a single-user application with automated agents as a resuscitation team for interaction.

All four virtual intervention group simulations or the entire e-learning course must be completed before entering Phase 3, or the participant will be dropped from the study.

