### **VR-related adverse events:**

AEs may occur during the use of VR, especially cybersickness (41). The following symptoms' incidence will be evaluated accordingly:

- Nausea and/or vomiting
- Dizziness
- Headaches
- Eye strain and fatigue (discomfort, blurred vision, reduced visual acuity)
- Physical effects (tripping, falling, and bumping into objects in the real world)

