| Learning method (participants' impression)                                     |                 |                      |
| - Learning progress                                                            |                 |                      |

|                                                           |                  |                      |
|-----------------------------------------------------------|------------------|----------------------|
| - Level of frustration                                    | Questionnaire 2  | 5-point Likert scale |
| - Level of enjoyment                                      |                  |                      |
| Participants' confidence in management of TCA             | Questionnaires 2 | 5-point Likert scale |
| Participants' performance                                 |                  |                      |
| - Participants' subjective impression                     | Questionnaires 2 | 5-point Likert scale |
| - Experts' impression                                     | Scoring sheet    | 5-point Likert scale |
| VR-related adverse events                                 | Questionnaire 2  | Incidence rate       |
| SUS                                                       | Questionnaire 2  |                      |
| - SUS score                                               |                  | 1 to 100             |
| - Adjective rating scale                                  |                  | 7-point Likert scale |
| Drop-out variables                                 |                  |                      |
| Training/studying with other non-study learning resources | Questionnaire 2  | Yes/no               |
| Insufficient preparation with assigned learning method    |                  | Yes/no               |

---

*ALS = advanced life support; AOI = area of interest; ATLS = advanced trauma life support; CPR = cardiopulmonary resuscitation; ERC = European Resuscitation Council; ETC = European Trauma Course; NASA-TLX = National Aeronautics and Space Administration Task Load Index; PHTLS = prehospital trauma life support; SUS = system usability scale; TCA = traumatic cardiac arrest; VR = virtual reality*

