### **Secondary objectives/outcomes:**

A two-sided generalized Wilcoxon test will also be used to compare times to critical actions, excluding the primary outcome. The number of participants who did not recognize and treat the underlying condition of the TCA, and the number of participants declaring the patient dead prematurely, will be compared between groups calculating the chi-square test. Protocol deviations will be analyzed separately for each protocol deviation listed in Table 2. The respective frequencies of each protocol deviation will also be compared between groups calculating the chi-square test. Fisher's exact test will be used if one or more expected cell frequencies are less than 5.

In addition, the Wilcoxon rank sum test will also be used to compare the gaze behavior (dwell-time in AOIs, fixation count and average fixation duration, and relative time when no AOI is illustrated) and the NASA-TLX scores (global and per objective) between randomized groups.

Furthermore, a multivariable Cox regression model (including an interaction term) will be used to determine the influence of gender on the primary outcome, and the potential modifying effect of gender on the training effect (= group effect). The HEXACO subscale and the Technology Readiness Score will also be included in the multivariable model to adjust for potential imbalances between the randomized groups.

The following Spearman correlation coefficients will be calculated corresponding to the remaining secondary objectives:

- Correlation of 5-point Likert scales between the frequency of playing classic video games and the primary outcome

5-point Likert scales, the incidence rate of VR-related AEs, and the SUS scores will be reported using descriptive statistics only.

Observations with missing data in the primary outcome measure will be excluded from statistical analyses. Boxplots will be used to illustrate calculations. A two-sided p-value of  $< 0,05$  will be considered statistically significant.

Due to the singular primary objective, no correction for multiple testing will be made. All secondary objectives are exploratory in nature and will be used to generate further hypotheses.

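### VR adverse-event incidence and usability are measured only in participants who finish VR training, and the exclusion for a missing primary outcome is not limited to analyses that use it

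*Protocol*

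**What the plan says.** **Who reaches the assessment.** Section 3.1.3 makes incomplete preparation a reason for withdrawal. Section 3.2 says "If participants do not complete the entire e-learning course or all four VR simulations, they will be dropped from the study". Section 3.2.2 repeats that the four simulations or the whole course "must be completed before entering Phase 3, or the participant will be dropped from the study".

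**Where adverse events come from.** Under its heading on VR-related adverse events, section 3.2.2 expects such events, cybersickness above all. It introduces a list (nausea or vomiting, dizziness, headache, eye strain, physical effects) with "The following symptoms' incidence will be evaluated accordingly". Table 3 in section 3.4.1 gives one source: "VR-related adverse events | Questionnaire 2 | Incidence rate". The SUS has the same source.

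**When that source is completed.** Section 3.2 says "each participant will be required to complete Questionnaire 2 (Additional file #3) immediately following the simulation session in Phase 3". The end of section 3.2.3 confirms this timing.

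**How the data are analysed.** In section 3.5, under the secondary outcomes, "the incidence rate of VR-related AEs, and the SUS scores will be reported using descriptive statistics only". Shortly afterwards, under the same heading, comes "Observations with missing data in the primary outcome measure will be excluded from statistical analyses". The protocol names no separate population for adverse events.

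**The concern.** VR exposure takes place in Phase 2, and its side effects are recorded only after Phase 3. Between the two stands a rule that removes everyone who did not finish the exposure. Those who could not tolerate the headset are the most informative cases for a tolerability estimate, and they are the ones removed. The published incidence would describe people who tolerated four sessions, while a reader would take it as the incidence among people given VR. Section 4.3 describes participation as free of risk apart from data disclosure, so objective 10 is the trial's main check on tolerability.

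The exclusion sentence in section 3.5 raises a second, smaller question. It stands among the secondary outcomes and names no analysis. Taken literally, a participant without a usable primary time also loses NASA-TLX, SUS and adverse-event data, none of which depends on that time.

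**Working it through.** **1. The plan's own figures.** Section 3.3 plans 30 per group at 80% power, for a probability of 0.71 and a two-sided level of 0.05. Noether's formula gives N = (1.960 + 0.842)² / (3 × 0.21²) = 59.3, so 30 per group. With 10% drop-out, 60 / 0.90 = 66.7, so 67. Both figures reproduce. The allowance is 67 − 60 = 7 participants, over both arms and for all causes.

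**2. The path of a VR user who stops for symptoms.** The participant starts VR in Phase 2 and does not finish the four simulations. The participant is dropped before Phase 3 (3.1.3, 3.2, 3.2.2), attends no session and receives no Questionnaire 2 (3.2, 3.2.3). Table 3 lists no other source, so the event is not recorded.

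**3. Size.** Let c be the VR completers, a the completers with symptoms, and s the VR users who stop because of symptoms.

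- Reported incidence = a / c
- Incidence counting those stoppers = (a + s) / (c + s)

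The value c = 30 is the planned group size. The values of a and s are assumptions, because the documents give none.

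| s | Reported | Counting stoppers | Difference |
|---|---|---|---|
| 0 | 5/30 = 16.7% | 5/30 = 16.7% | 0 |
| 1 | 5/30 = 16.7% | 6/31 = 19.4% | 2.7 points |
| 3 | 5/30 = 16.7% | 8/33 = 24.2% | 7.6 points |

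An outer bound puts all 7 expected drop-outs in a VR arm of 34, all for cybersickness: reported 5/27 = 18.5%, against 12/34 = 35.3%.

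**4. Direction.** Now let t further VR users stop for other reasons without symptoms. Incidence among starters is (a + s) / (c + s + t). The reported figure is too low only if s / (s + t) exceeds a / c, that is, if symptoms are commoner among stoppers than among completers. With s = 0 and t = 3, incidence among starters is 5/33 = 15.2%, and the reported 16.7% is slightly too high. With s = 1 and t = 2, it is 6/33 = 18.2%, and the reported figure is too low.

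**5. What the exclusion sentence contributes.** Delete it and repeat step 2. The stopper still never receives Questionnaire 2, and the reported rate is still 5/30.

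**6. Whom the exclusion sentence can affect.** Scenario failures and premature declarations of death are censored at 15 minutes (3.2.4, 3.5), so they are not missing. Drop-outs before Phase 3 have no assessment data to lose. What remains is mainly a participant who attended Phase 3 and completed Questionnaire 2 but whose recording yields no primary time.

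**The case against.** **Few may stop for symptoms.** The 10% allowance covers all causes. Predisposition to cybersickness is an exclusion criterion (3.1.2), and withdrawal needs no reason (4.2). This stands. It is why the range starts at no stops and why the size is conditional. Entry screening lowers the risk but does not remove it, and the protocol itself expects such events.

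**Some dropped participants may reach Questionnaire 2.** Table 3 lists outside training, a drop-out variable, under that questionnaire, so those participants would have answered it. For incomplete preparation the source cell is blank in the text at hand. Even if Questionnaire 2 was meant there too, sections 3.2 and 3.2.2 remove non-completers before the session that the questionnaire follows.

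**The exclusion sentence may be narrower than it looks.** It does not contain the word *all*. The sentence before it treats adverse events and SUS as descriptive only. The Cox model and the Spearman correlation, which use the primary outcome, stand in the same section and could explain its position. This reading is possible, so the point about the sentence is one of ambiguity.

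**A stronger reading.** A reader might infer that the exclusion sentence is what removes the adverse events of VR users who stop. Step 5 shows otherwise: the loss comes from the drop-out rule together with the timing of Questionnaire 2.

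**The outcomes are exploratory, and analysis sets may be left to a statistical analysis plan.** The first part is true and limits the weight of the point. On the second, no analysis plan can recover data that the protocol's schedule does not collect.

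**Conclusion.** The point holds for data collection. As scheduled, objective 10 and the SUS are obtained only from VR participants who finish all four simulations and attend Phase 3. Incidence is understated if symptoms are commoner among those who stop than among completers. Under the stated assumptions the gap runs from nothing to 7.6 percentage points with three symptomatic stops, and it is larger only if drop-out is concentrated in the VR arm for this reason. The SUS probably flatters the system as well, if people who stop would rate it lower; the documents give nothing to quantify that.

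The exclusion sentence is a lesser, separate matter. Its scope is unclear, and its broad reading would discard valid secondary data from a small group. It should not be blamed for the missing cybersickness cases. Neither part touches the primary comparison or the sample size.

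**What to change.** 1. Have VR participants complete the existing symptom list at each VR session, or at withdrawal if they stop. Add this source to Table 3. Report incidence among all participants who started VR, with the number who stopped and their reasons. Offering the SUS items at withdrawal would close the same gap for usability.
2. Reword the exclusion sentence so that it covers only analyses that use the primary outcome. Analyse each secondary outcome in all randomised participants with data on it.

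The cost is small. A questionnaire section that already exists is used earlier, and section 3.6.1 already places a study team member with participants in Phase 2. Denominators will differ slightly between tables and should be printed in each.

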## 3.6 Materials

### 3.6.1 VR Headset

For this study, participants in the intervention group will be provided with a VR headset, the HTC VIVE Focus 3 with two controllers. The appropriate software will be pre-installed and ready to use.

A study team member will be present during Phase 2 to assist with any technical difficulties.

### 3.6.2 Eye-tracking glasses

Video recordings will also be made from the perspective of the team leader using eye-tracking glasses, Tobii Pro Glasses 3.0, in addition to the conventional cameras in the simulation center.

Furthermore, eye movements will be recorded at a rate of 50 Hz. The data will be analyzed using the Tobii Pro Glasses Analyzer software. The area of visual attention detected by the glasses is marked with a circle in the video recordings.

### 3.6.3 E-learning platform

Moodle, the e-learning platform of the MedUni Vienna, is used to teach relevant content in the control group and is available to participants free of charge.

### 3.6.4 Video editing

Video editing will be done using the DaVinci Resolve 18 software.

## 4 PROTECTION OF HUMAN SUBJECTS

### 4.1 Informed consent

Study participants will be recruited as described in Section 3.1. Their participation is therefore voluntary. Prior to participation in the study, a member of the study team will provide detailed information about the potential benefits and disadvantages, procedure, and data used in this study. This explanation will also be recorded in writing on the informed consent form (Additional file #1). Study participation will only occur after written informed consent has been given.

### 4.2 Patient withdrawal

Participants may withdraw from the study at any time without giving a reason.

### 4.3 Ethical considerations and risk-benefit-evaluation

Since this is a comparative study of different learning methods, there is no risk to the study participants. The only risk is the disclosure of sensitive information about them, which is minimized by pseudonymization and access restrictions.

Further hypotheses can be generated from the results of this study.

## APPENDIX

| Document reference number | Title                  |
|---------------------------|------------------------|
| Additional file #1        | Informed consent       |
| Additional file #2        | Questionnaire 1        |
| Additional file #3        | Questionnaire 2        |
| Additional file #4        | Scoring                |
| Additional file #5        | Bulletin board posting |
